### **6.3. Subject Withdrawal**

Subjects may be withdrawn from study for any of the following reasons:

1. The subject withdraws from the study on his/her own volition.
2. The subject develops Hepatitis B, Hepatitis C, or HIV as determined by a positive result on a test for HBsAg or on a NAT for HCV or HIV RNA, or the appropriate serological tests for these viruses.
3. The subject has a serious adverse event (SAE) while participating in the study and, at the discretion of the site investigator, is discontinued.
4. The subject becomes pregnant while participating in the study. Any subject that becomes pregnant while participating in the study will not receive any further infusions of GAMMAPLEX.
5. The investigator may withdraw subjects at anytime if they feel it is not in the subject's best interest to continue in the study.

If a subject's Day 1 blood sample results from the central laboratory (for Laboratory A, Laboratory B tests or for the other protocol required blood tests) are out of range, the subject will be withdrawn from the efficacy analysis only. These subjects will still be included in the safety analysis and will therefore continue to attend the follow-up visits. Subjects withdrawn from the efficacy analysis will not be eligible to receive any further courses of GAMMAPLEX.

If a subject receives any of the study product and withdraws, all of the assessments scheduled on Day 32 and the End of Study visit must be done, if possible. For subjects who received more than 1 course of GAMMAPLEX before withdrawal, every effort must be made to complete the assessments scheduled for the End of Study visit.

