If the subject is enrolled within 14 days of screening, all medications the subject is taking at the time of screening may be continued through the completion of the second infusion, including corticosteroids; however, the dose must remain unaltered through Day 9 unless some condition of the subject requires a change. If possible, doses of corticosteroids or other immunosuppressant medications should remain constant until Day 32 (see Section 6.1). All concomitant medications will be recorded on the CRFs.

If the subject is not enrolled within 14 days of screening, it should be noted that doses/regimen of corticosteroid must have been stable for 2 weeks prior to Day 1; and doses/regimen of azathioprine, cyclophosphamide, and attenuated androgens must have been stable for 2 months prior to Day 1. Changes to the dosage of these medications should be avoided as mentioned above. In addition subjects are not to receive an IGIV preparation or an investigational agent or

any blood, blood product or blood derivative within 1 month prior to Day 1, and receipt of any live virus vaccine and Rituximab is not allowed within 3 months prior to Day 1.

Administration of corticosteroids to decrease adverse reactions to the infusion may not be given before the IGIV infusions. However, pre-medication with analgesic or antihistamine drugs is permissible if required.

No blood products, including IGIV (other than GAMMAPLEX in accordance with the protocol), may be given during the study until the End of Study visit (viral safety visit approximately 3 months after the last dose of GAMMAPLEX).

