**5.3.1.3. Follow-Up Visits for First Treatment Course (Days 3, 5, 9, 14, 21 and 32)**

At each visit the following will be done:

*Interval Medical History*

Any changes from the previous medical history on Day 1 should be recorded in the CRF.

*Physical Examination*

A physical examination will be performed at every visit and the results recorded in the CRF.

*Vital Signs*

Vital signs assessed by qualified personnel will be entered in the CRF at the Visits on Days 3, 5, and 9 only.

*Blood Samples for Laboratory Tests*

- Blood samples for Laboratory A will be drawn at each of the follow-up visits (Days 3, 5, 9, 14, 21, and 32).
- Samples for Laboratory B will be drawn on Days 3 and 9 and Day 32.
- Serum for IgG levels will be drawn at each visit
- Samples for Direct Coombs' Test will be taken on Day 5 and Day 14. (see Section 9.3.2). Samples for LDH, haptoglobin, and urine hemosiderin will also be taken on Day 5 and Day 14.

- NAT for Parvovirus B19 on Day 9 and Day 32.
- NAT for HCV and HIV on Day 32.
- Serology for HIV1 and HIV2, HCV, HBsAg on Day 32. Any seroconversion should be followed up.
- A reserve sample will be taken at each visit

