## **8. ASSESSMENT OF EFFICACY**

### **8.1. Primary Efficacy Variable**

The primary efficacy variable will be the percent of subjects attaining a platelet count of  $\geq 50 \times 10^9/L$  by Day 9 (the 7th day after completing the second infusion).

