### **8.2. Secondary Efficacy Variables**

There will be 2 secondary efficacy variables:

- Duration of time for which the platelet count remains  $\geq 50 \times 10^9/L$  following the first treatment course of GAMMAPLEX
- Changes in the signs of any bleeding/hemorrhage up to Day 32 (see Appendix 1 for grading criteria)

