### **9.2. Vital Signs**

Vital sign values will be obtained as detailed in Section 5.3.1.2. Any clinically significant changes in vital signs will be reported as AEs as described in Section 9.1.1.2. Clinically significant hypotension (i.e., a  $\geq 30$  mmHg drop in systolic blood pressure accompanied by clinical findings/symptoms, or a systolic blood pressure of  $\leq 70$  mmHg) and/or anaphylactic reactions (significant hypotension with generalized hives/angioedema or bronchospasm) warrant discontinuation of the infusion and administration of appropriate supportive care as deemed necessary by the investigator (may include epinephrine, antihistamine, corticosteroids, supplemental oxygen, expansion of the plasma volume as necessary, etc.). These occurrences must be recorded in the CRF as AEs. At the discretion of the investigator, the subject may be withdrawn from the study, but will complete the follow-up visits. Before listing changes in vital signs as AEs, each change should be assessed for clinical relevance.

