### 10.2. Analysis Population

Any subject who started treatment with GAMMAPLEX and whose central laboratory results taken prior to infusion on Day 1 are within specified protocol parameters, will be included in the intent-to-treat (ITT) population for analysis of efficacy and safety. Any subject whose central laboratory results from Day 1 are outside of the required parameters, will be included in the safety analysis only.

Additionally, subjects aged 6 to 17 years (applicable only to subjects enrolled before implementation of Protocol Version 7) will be analyzed separately from the remaining samples for any differences in response to treatment. This subset will be analyzed in the same manner as the total sample.

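### Section 6.3 does not ask most subjects who withdraw early for the platelet counts through Day 9 that decide the primary endpoint

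*Protocol*

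**What the plan says.** Section 6.3 lists reasons for withdrawal, including the subject's own decision, a serious adverse event and the investigator's judgement at any time. For a subject who has received study product and withdraws, it then says that "all of the assessments scheduled on Day 32 and the End of Study visit must be done, if possible". No earlier visit is named.

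Section 8.1 defines the endpoint: "The primary efficacy variable will be the percent of subjects attaining a platelet count of" at least 50 × 10⁹/L by Day 9. Section 5.3.1.3 supplies the data: "Blood samples for Laboratory A will be drawn at each of the follow-up visits", that is, on Days 3, 5, 9, 14, 21 and 32. Section 10.2 puts into the ITT population "Any subject who started treatment with GAMMAPLEX and whose central laboratory results taken prior to infusion on Day 1 are within specified protocol parameters". Later withdrawal does not remove a subject from it.

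Section 9.2 has its own rule for clinically significant hypotension or an anaphylactic reaction: "the subject may be withdrawn from the study, but will complete the follow-up visits".

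**The concern.** The counts that can show a response fall on Days 3, 5 and 9. The Day 32 count cannot. A subject who leaves inside that window without having reached 50 remains in the denominator, and the protocol asks for nothing that could still settle the outcome. An analysis plan can say how a missing count is scored, but it cannot recover a sample that was never drawn, so the list of visits requested after withdrawal is for the protocol to get right.

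The document is also inconsistent. A site handling a withdrawal after hypotension or anaphylaxis finds the short list in 6.3 and the full follow-up schedule in 9.2.

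At stake is power in a small single-arm trial where one subject can change the result. There is a lesser cost to the secondary variable in Section 8.2, "Duration of time for which the platelet count remains" at or above 50 × 10⁹/L, because the Day 14 and Day 21 counts are not requested either.

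**Working it through.** **Counts requested.** Take a subject below 50 on Day 3 who withdraws just afterwards, for a reason outside 9.2.

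- In-window counts still to come: Days 5 and 9. Requested under 6.3: 0 of 2.
- First-course counts still to come: Days 5, 9, 14, 21 and 32. Requested: 1 of 5.
- If the subject withdraws before Day 3, three in-window counts remain and again none is requested.
- If the subject was already at 50 or above on Day 3, the primary outcome is settled. A later fall is then located only within 32 − 3 = 29 days, against a longest scheduled gap of 32 − 21 = 11 days.

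**The stated minimum of 31.** Section 10.1 gives no expected response rate, so 31 cannot be reproduced as such. As a plausibility check, the one-sample normal formula with null rate 0.60, one-sided 5% and 80% power is

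n = [(1.645·√(0.6·0.4) + 0.842·√(p(1−p))) / (p − 0.6)]²

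It gives 33 at p = 0.80 and 30 at p = 0.81, so 31 fits an assumed rate a little above 0.80.

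**Success threshold.** Section 10.3.1 requires the one-sided 95% lower bound to exceed 0.60. The protocol text names no interval method, so I assume the exact bound, BetaInv(0.05; x, 31 − x + 1):

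- x = 23: 0.582, fails
- x = 24: 0.617, passes

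A Wilson bound also needs 24. A simple Wald bound needs 23.

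**Power.** Let w subjects lack a deciding count and be scored as non-responders. Power = P(Bin(31 − w, p) ≥ 24). The true rates p and the values of w are assumptions.

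| True rate p | w = 0 | w = 1 | w = 2 |
|---|---|---|---|
| 0.80 | 0.730 | 0.607 | 0.463 |
| 0.85 | 0.918 | 0.847 | 0.738 |
| 0.90 | 0.990 | 0.974 | 0.936 |

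With the Wald threshold of 23, one such subject takes power from 0.849 to 0.761 at p = 0.80.

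**What retention recovers.** Suppose the one subject is followed through Day 9 and responds with probability q. At p = 0.80,

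power = q·P(Bin(30, 0.80) ≥ 23) + (1 − q)·P(Bin(30, 0.80) ≥ 24) = 0.7608q + 0.6070(1 − q)

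- q = 0.80: 0.730, a gain of 12.3 points
- q = 0.50: 0.684, a gain of 7.7 points
- q = 0: 0.607, no gain

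**The case against.** The strongest case on the other side is that the gap is narrow.

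- **Few reasons act before Day 9.** After Day 1, HBsAg, HCV and HIV are next tested on Day 32, and no pregnancy test is scheduled after Day 1. A subject who leaves by choice cannot be made to attend. That leaves serious adverse events and investigator decisions outside 9.2, plus volunteers who would still agree to a blood draw. Section 9.1.1.4 requires adverse events to be followed, but does not name platelet counts. This stands and limits how often the gap matters.
- **Another reading of 6.3.** The Day 32 assessments could be taken as a set performed at withdrawal, which would give a count inside the window. The text does not exclude this, nor does it forbid earlier visits. Even so, it requests no later in-window count, and the ambiguity itself needs clearing up.
- **Re-estimation.** 31 is a minimum, and Section 10.1 provides for re-estimation to 80% power from the rate seen at 27 evaluable subjects. Early losses scored as failures would lower that rate and raise the final number. This may offset part of the loss.

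A reader might infer four stronger points that the document does not support:

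- **The short list applies to every withdrawal.** Section 9.2 says otherwise for hypotension and anaphylaxis.
- **The subject is a non-responder by the text.** The protocol states no scoring for a missing count. That is properly left to the analysis plan.
- **Subjects who do not count toward efficacy are followed better than those who do.** Section 6.3 does say of subjects with out-of-range Day 1 results: "These subjects will still be included in the safety analysis and will therefore continue to attend the follow-up visits". But they leave the efficacy analysis only, not the study, so their attendance is no rule for withdrawn subjects.
- **The blood-product ban in Section 5.3.1.1 needs an urgent-bleeding exception.** It does say: "No blood products, including IGIV (other than GAMMAPLEX in accordance with the protocol), may be given during the study". But no text blocks urgent treatment or makes it a reason to withdraw. Section 5.3.1.4 allows further GAMMAPLEX between Days 9 and 32 after discussion with the medical monitor and sponsor. Relaxing the ban would also complicate the viral-transmission assessment.

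**Conclusion.** The point holds in a limited form. Outside the group covered by 9.2, a treated subject who withdraws before Day 9 while below 50 × 10⁹/L stays in the ITT population with no remaining in-window platelet count requested. For the 9.2 group, the two sections give different lists.

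The effect is zero without early withdrawal, and the protocol gives no withdrawal rate. If missing counts are scored as non-response, the error is conservative and does not favour the product. The cost is then power: 12.3 points (0.730 to 0.607) for one subject at n = 31, assuming an exact bound and a true rate of 0.80. Retention recovers between none and all of that, depending on how often such subjects would have responded. The loss is smaller at higher true rates and may be partly offset by re-estimation. This is an inexpensive improvement worth making, and not a threat to the validity of a positive result.

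**What to change.** In Section 6.3, replace the sentence on assessments after withdrawal with:

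> A subject who receives any study product and withdraws will be asked, if he/she agrees, to complete the remaining scheduled follow-up visits, at minimum the Laboratory A platelet counts through Day 9, plus the Day 32 and End of Study assessments.

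Align Section 9.2 with it, so that one rule covers every withdrawal. No change to the blood-product rule is proposed.

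The cost is the wording, plus visits that are already scheduled. For a subject withdrawn after Day 3 these are at most four (Days 5, 9, 14, 21), or two if only the minimum is done. Each takes 2 mL of blood if only Laboratory A is drawn. The downside is this modest burden on people who have chosen, or been advised, to leave, which is why the request depends on their agreement.

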### **6.4. Study Termination**

In the event of a trend in the safety data that would indicate any concern for the safety of the subjects, the sponsor, medical monitor and the study site investigator will consider if the study should be terminated. The appropriate IRBs/IECs and regulatory authorities will be informed of any decision to terminate the study earlier than planned.

## **7. DESCRIPTION OF TREATMENT ADMINISTERED**

### **7.1. Investigational Product**

#### **7.1.1. Identification and Batch Numbers**

The batch numbers of GAMMAPLEX will be documented in the Certificate of Analysis that will be filed in the Trial Master File. The actual batch number will be documented in the CRF for

each infusion. A list of all batches used and the subjects who received them will be included in the final study report. At least 2 batches of GAMMAPLEX will be used for this study.

#### **7.1.2. Packaging and Labeling**

GAMMAPLEX will be manufactured, packed, and labeled by BPL. The product will be supplied in glass bottles (100 mL per bottle), and each bottle will be packed in a box. The label will include contact information for BPL and the identity, total quantity and volume, concentration, batch number, expiry date, and storage requirements of the product. A statement (in bold type) that the investigational product is not compatible with other fluids will also be on the label. The label on the bottle will be a 2-part, tear-off label. One part must be attached to the subject's source documents when the bottle is used for the infusion.

#### **7.1.3. Conditions for Storage and Use**

GAMMAPLEX should be stored in a secure area of limited access, preferably in a locked cupboard, protected from light, and maintained at a temperature of 36°F to 77°F (2°C to 25°C). GAMMAPLEX must not be frozen.

### **7.2. Investigational Treatment**

#### **7.2.1. Dose Schedule and Rationale**

All eligible subjects will receive an infusion of 1 g/kg of GAMMAPLEX on each of 2 consecutive days (Day 1 and Day 2). This will be the first treatment course of GAMMAPLEX. The dose of 1 g/kg/day on 2 consecutive days is consistent with recommendations for the use of other IGIV products for ITP [15-17,21].

A small variation in the amount of GAMMAPLEX to be infused will be allowed for those subjects whose calculated dose would necessitate disposing of a significant amount of GAMMAPLEX following the infusion. In order to avoid unnecessary waste, the total volume of GAMMAPLEX infused may be adjusted by the lesser of either 10 mL or 2% of the total volume infused.

If the platelet count is not maintained for the desired length of time after the first course of GAMMAPLEX, and at the discretion of the study investigator and subject/guardian, subjects may receive up to 2 further courses of GAMMAPLEX at the same dosage regimen as course 1 between Day 32 and the End of Study visit.

#### **7.2.2. Product Preparation**

Before use, all bottles must be inspected visually for discoloration, particles, and fibers; if the contents of a bottle are cloudy or contain particulate material, they must not be used. GAMMAPLEX is to be at room temperature when it is infused.

One of two methods of administration may be used:

*From the bottle*

Administration of GAMMAPLEX must be started immediately after breaking the seal of the bottle. A qualified member of staff must administer GAMMAPLEX by using a standard administration kit. **For any single treatment course, all GAMMAPLEX given to any 1 subject must be from the same batch.**

*From an infusion bag*

GAMMAPLEX must be pooled under aseptic conditions into a polyvinyl chloride infusion bag by a qualified member of the site staff or pharmacist working to local standard operating procedures (SOPs). The infusion must be started as soon as possible, and in any case within 2 hours, after pooling into the infusion bag.

All infusions will be administered directly from the infusion bag by using a standard administration kit. The infusion bags will be labeled with the manufacturer's lot/batch number, subject number, protocol number, and the expiration date. **For any single treatment course, all GAMMAPLEX given to any 1 subject must be from the same batch.**

**7.2.3. Method of Administration**

All subjects should be adequately hydrated before infusion. If clinical assessment suggests the subject is dehydrated, intravenous fluids may be given before the scheduled infusion is started. Infusions will be administered by trained personnel under the direct supervision of the responsible investigator or his/her designee.

GAMMAPLEX will be administered intravenously (peripheral or central vein) through an infusion line with a 15- to 20-micron filter. Mixing and administration of any other product (including normal saline) with GAMMAPLEX is strictly prohibited.

All infusions will be initiated at a rate of 0.01 mL/kg/min for the first 15 minutes; if tolerated, the rate of infusion must be advanced as shown in Table 3. Lack of tolerance at any of these rates must be recorded as an AE at that rate. If a subject has the same AE at the same rate twice, and those AEs have been recorded, then subsequent infusion rate escalations should be halted at the previously highest tolerated rate.

**Table 3 Starting, Incremental, and Maximum Infusion Rates**

| Infusion     | GAMMAPLEX Infusion Rate |            | Elapsed Time
(min)    |
|--------------|-------------------------|------------|--------------------------|
|              | (mL/kg/min)             | (mg/kg/hr) |                          |
| Starting     | 0.01                    | 30         | 0–15                     |
| Increment to | 0.02                    | 60         | 16–30                    |
|              | 0.04                    | 120        | 31–45                    |
|              | 0.06                    | 180        | 46–60                    |
|              | 0.08                    | 240        | 61 until end of infusion |

If any AE of moderate or severe intensity occurs (see Table 4), the rate of the infusion at which this AE occurred will be recorded, and the infusion rate will be reduced to one-half the rate of that at which the event was observed; or if necessary, to a keep open (TKO) rate until symptoms subside. The infusion may then be resumed at a rate tolerated by the subject.

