| Tachycardia                                                                                                                                                       | HR = 1.2 to 1.4x baseline                              | HR = 1.41 to 1.6x baseline                                                                                   | HR > 1.6 x baseline                                                                                                                           |
| Arrhythmia                                                                                                                                                        | Occasional, asymptomatic
(not-present pre-infusion) | < 1 per minute, and
asymptomatic                                                                          | > 1 per minute, or
symptomatic                                                                                                             |
| Hypotension (% fall in
systolic or diastolic blood
pressure in mmHg (from
either pre-infusion
measurement, whichever is
lower – see Section 9.2.   | 10 to 15% b                                 | 16 to 25% b                                                                                       | > 25% b                                                                                                                            |
| Hypertension (% rise in
systolic or diastolic blood
pressure in mmHg (from
either pre-infusion
measurement, whichever is
higher – see Section 9.2. | 20 to 25% b                                 | 26 to 30% b                                                                                       | > 30% b                                                                                                                            |
| ALLERGIC                                                                                                                                                   | Pruritus without rash                                  | Pruritic rash; tachypnea
1.3 to 2 x the higher
baseline, chest tightness
suggestive of bronchospasm | Urticaria; tachypnea > 2 x
the higher baseline,
bronchospasm,
laryngospasm, angioedema,
circulatory shock (severe
hypotension) |

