| Nausea                                                                                                                                                            | Discomfort, but does not
require medication         | Can take fluids without
antiemetic medication                                                             | Little or no oral intake
and/or requires antiemetic
medication                                                                          |
| Vomiting                                                                                                                                                          | 1 episode                                              | 2 to 3 episodes                                                                                              | > 3 episodes                                                                                                                                  |

a This table applies to AEs associated with an infusion that occur during an infusion and/or up to 60 minutes after an infusion. The infusion rate at which the AE is observed will be recorded.

b If not accompanied by an increase in heart rate and subject is assessed as being comfortable or sleeping, blood pressure changes of this magnitude may be classified by the investigator as physiologic and not considered an AE.

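### Sections 7.2.3 and 9.2 prescribe different infusion actions for the same hypotensive or anaphylactic reaction, and the protocol does not say which prevails

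*Protocol*

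**What the plan says.** **Section 7.2.3, text below Table 3.** The trigger is general: "If any AE of moderate or severe intensity occurs (see Table 4), the rate of the infusion at which this AE occurred will be recorded". The action follows: "the infusion rate will be reduced to one-half the rate of that at which the event was observed". Where needed, the rate may be lowered further, to keep-open (TKO), while the symptoms last. Restarting is then permitted but not required: "The infusion may then be resumed at a rate tolerated by the subject". The rule has no exception and no stopping branch, and it does not mention Section 9.2.

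**Table 4 (Section 9.1.1.2).** A fall in systolic or diastolic pressure is Moderate at 16 to 25% and Severe above 25%. The Severe cell of the allergic row lists urticaria, marked tachypnea, bronchospasm, "laryngospasm, angioedema" and circulatory shock. Footnote b is attached to all the blood pressure grades. If heart rate does not rise and the subject is comfortable or asleep, "blood pressure changes of this magnitude may be classified by the investigator as physiologic and not considered an AE".

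**Section 9.2.** Clinically significant hypotension is a systolic drop of at least 30 mmHg with clinical findings or symptoms, or a systolic pressure of 70 mmHg or less. An anaphylactic reaction is significant hypotension with generalized hives/angioedema or bronchospasm. These events "warrant discontinuation of the infusion and administration of appropriate supportive care as deemed necessary by the investigator", and they must be entered in the CRF as adverse events.

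**The concern.** The events named in 9.2 appear to lie inside the trigger of 7.2.3. If they do, staff facing one of the most serious infusion reactions hold two instructions that cannot both be carried out: run at a reduced or keep-open rate, or discontinue. The infusion rule stands in the administration section and the stopping rule in the section on vital signs, and the trial runs at approximately 25 sites in three countries. Two sites could handle the same reaction differently while each followed the protocol.

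The first consequence is for subject safety. The second is for the data: the dose delivered in the affected infusion would depend on which section the site applied. The recording conflict bears on the tabulated number of infusions with an adverse event during infusion or within 72 hours (Sections 9.1 and 10.4.1). Safety at the dose used is a secondary objective (Section 4.2).

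**Working it through.** The protocol states no figure to reproduce here. The check is whether an event that meets 9.2 also meets the trigger of 7.2.3, that is, at least Moderate in Table 4.

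**Inputs.** 9.2 thresholds: systolic fall of at least 30 mmHg (with symptoms), or systolic pressure of 70 mmHg or less. Table 4 cut-offs: Moderate 16 to 25%, Severe above 25%. B is the pre-infusion systolic pressure. Table 4 takes the lower of the two pre-infusion readings. Section 9.2 does not name its reference reading, so I assume the same B.

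**Formulas.** Percent fall for a 30 mmHg drop = 100 × 30/B. Percent fall to 70 mmHg = 100 × (B − 70)/B.

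| B (mmHg) | 30 mmHg fall | Grade | Fall to 70 mmHg | Grade |
|---|---|---|---|---|
| 80 | 37.5% | Severe | 12.5% | Mild |
| 90 | 33.3% | Severe | 22.2% | Moderate |
| 100 | 30.0% | Severe | 30.0% | Severe |
| 120 | 25.0% | Moderate | 41.7% | Severe |
| 140 | 21.4% | Moderate | 50.0% | Severe |
| 160 | 18.75% | Moderate | 56.25% | Severe |
| 180 | 16.7% | Moderate | 61.1% | Severe |

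**Boundaries.**
- A 30 mmHg fall is at least Moderate while 30/B ≥ 0.16, so B ≤ 30/0.16 = 187.5.
- A fall to 70 mmHg is Severe when (B − 70)/B > 0.25, so B > 70/0.75 = 93.3. It is at least Moderate from B = 70/0.84 = 83.3.
- Larger falls only raise the percentage. Table 4 also grades the diastolic fall, which can raise the grade but not lower it.

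Between about 94 and 187 mmHg, therefore, any event meeting either 9.2 hypotension threshold also triggers 7.2.3. The lower limit is conservative, since 84 would do for a Moderate grade. Exclusion 17 sets a systolic limit of 160 mmHg, which is inside the range.

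**Anaphylaxis.** No arithmetic is needed. The accompanying signs in the 9.2 definition (hives, angioedema, bronchospasm) are in the Severe allergic cell of Table 4, so 7.2.3 is triggered as well.

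**Precedence.** Section 7.2.3 cites Table 4 only. The blood pressure rows of Table 4 cite 9.2, but within the description of the pre-infusion measurement. The allergic row does not cite it. Section 9.2 refers back to 9.1.1.2 for reporting. None of these says which infusion action prevails.

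**Footnote b against 9.2.** The symptomatic limb of 9.2 and anaphylaxis are largely outside footnote b, because the subject would not be comfortable. The limb at 70 mmHg or below requires no symptoms. A subject asleep at that pressure with no rise in heart rate meets footnote b (may be classed as not an adverse event) and 9.2 (must be recorded as one). If footnote b is used, there is no adverse event to trigger 7.2.3 either, while 9.2 still says the event warrants discontinuation.

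**The case against.** The strongest reply is that 7.2.3 is the general rule, covering headache and chills as much as shock, and 9.2 is the specific rule for a few grave events, so the specific one naturally prevails. Infusions run under the direct supervision of the investigator or a designee, who would be expected to read them so. That reading is reasonable, but the protocol does not state it, and precedence should not have to be inferred during an acute reaction.

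It can also be said that the sections are linked. That is true: Table 4 cites 9.2, 9.2 cites 9.1.1.2, and the vital signs text for infusion visits (Section 5.3.1.2) cites both. A reader might infer that there is no cross-reference at all, and that would be wrong. What is missing is a link that carries the stopping rule into 7.2.3 and the allergic row.

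Other stronger readings also fail:
- **Mandatory resumption against permanent stopping.** Resumption in 7.2.3 is only permitted, and 9.2 does not say that discontinuation is permanent. The conflict is in the immediate action, where the rate reduction is worded as an instruction.
- **Percent against mmHg as a conflict of its own.** Section 7.2.3 gives Moderate and Severe the same action, so the grade assigned to a 30 mmHg fall changes nothing. The conversion only shows that the two rules overlap.
- **All Severe allergic signs affected.** Bronchospasm, laryngospasm or angioedema without hypotension is outside the wording of 9.2 and carries one rule only.
- **The repeat-event sentence.** The text beginning "If a subject has the same AE at the same rate twice, and those AEs have been recorded" governs further escalation. The severity rule follows it, below Table 3, so the sentence is not evidence that severity is ignored.

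On footnote b, 9.2 does ask that changes be assessed for clinical relevance before being listed as adverse events. But it has already defined 70 mmHg or below as clinically significant, so that sentence does not remove the conflict.

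**Conclusion.** The point stands for the events that 9.2 names. Within about 94 to 187 mmHg pre-infusion systolic pressure, its hypotension criteria also satisfy the trigger of 7.2.3, and its anaphylaxis definition does so through the allergic row. The two sections then give different immediate infusion actions with no stated precedence. The recording conflict with footnote b is real but narrow: a systolic pressure of 70 mmHg or below, no rise in heart rate, and a subject who is comfortable or asleep.

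This rests on using the same pre-infusion reading for both sections and on the literal trigger of 7.2.3. The documents give no basis for estimating how often such events would occur. No effect on the primary endpoint is shown, and a count of discontinued infusions is not among the listed adverse event summaries in Section 10.4.1. The case for correction is subject safety and uniform conduct across sites. No view is taken on which clinical rule is right.

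**What to change.** Reconcile the rule below Table 3 in 7.2.3, Table 4 with its footnote b, and 9.2, so that each event has one infusion action and one recording rule:

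1. State in 7.2.3 whether its rate rule applies to events that meet the 9.2 definitions.
2. Cross-refer to 9.2 from 7.2.3 and from the allergic row of Table 4.
3. State whether footnote b can be applied to an event that meets a 9.2 definition.

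The sponsor and medical monitor decide the clinical content. The cost is a wording amendment to two sections and one table with its footnote, with whatever approvals Section 14.1 requires, and a notice to sites. It adds no procedures or subjects.
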